### 3.5. Speech

A clinical evaluation will be carried out by a speech therapist specialized in the area of Orofacial Motricity, to check for possible improvement in speech. For this, the Glatzel test will be used to measure the degree of nasal patency and the functional symmetry of the upper airways both at rest and in function. Specifically in the functional evaluation, its usefulness is linked to the verification of the existence of nasality or hyponasality before vowels elicited by the patient.

### 3.6. Presence of bruxism

The bruxism questionnaire will be delivered to parents or guardians, which will be completed prior to treatment and afterwards. The questionnaire contains 4 questions regarding the perceived presence of bruxism, and 5 questions for the dentist to answer, based on a clinical observation. All questions have the options “yes” or “no.” The more times the word “yes” is chosen, the greater the risk for bruxism is.

### 3.7. Sleep quality

A Pediatric Sleep Quality Questionnaire will be delivered to parents or guardians, and it will be completed prior to treatment and afterwards. The questionnaire contains 44 questions regarding sleep quality. All questions have the options “yes” or “no.” The more times the word “yes” is chosen, the worse is the sleep quality.

### 3.8. Statistical analysis

The data will be tabulated and processed with the software GraphPad PRISM version 7.0. The values will be tested for normality by the Kolmogorov–Smirnov test, and will be expressed as mean and standard deviation if Gauss curve is assumed. For the comparison between the groups, the *t* test will be carried out, considering a level of significance of 0.5% (*P* < .05). No loses greater than 5% of the sample are expected.

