### 2.2. Participants

A triage of individuals between 4 and 17 years old, diagnosed with sleep bruxism, will be carried out at the dentistry clinic of the Catholic University of Uruguay. Patients will already be in treatment for other conditions at the clinic, what will facilitate recruitment. It is believed that the need for treatment of bruxism before major pain symptoms or dental wear will help to improve adherence to the trial.

Inclusion criteria:

Children in the mixed dentition phase (permanent incisors and first molars erupted);Or adolescents with an established permanent dentition.

Exclusion criteria:

People with dental caries;Those taking medications, such as inflammatory agents, muscle relaxants, corticosteroids, anticonvulsants, and antidepressants;Those with chronic diseases that affect muscles or motor coordination, and those who do not cooperate during the evaluation will be excluded from the study;Children with cerebral palsy;Patients whose guardians do not sign the informed consent or the participant who does not sign the assent form.

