### 2.4. Sample calculation

The sample was calculated to detect a significant difference between PBM and MFT with 80% power and a significance level of 5%, considering the oxygen saturation index. Based on the study by Aarab et al^[19]^ to detect a difference in saturation index, with an effect size of 0.53, the minimum number per group should be 23 participants per group (Fig. 2).

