**Figure 2. F2:**
[figure not shown]
Sample size calculation. Analysis: A priori: Compute required sample size; Input: Tail(s) = One; Effect size dz = 0.5373031; *α* err prob = 0.05; Power (1-*β* err prob) = 0.8; Output: Noncentrality parameter *δ* = 2.576815; Critical t = 1.7171444; Df = 22; Total sample size = 23; Actual power = 0.8027361.^[19]^

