### 3.1. Oximetry

Recorded sleep oximetry monitoring has high specificity and sensitivity for the diagnosis of respiratory disorders in children. This is the primary outcome of the study.

A portable pulse oximeter that includes Masimo SET® Measure-through Motion and Low Perfusion™ pulse oximetry under motion and low perfusion conditions. Nocturnal oximetry will be performed prior to treatment and post treatment. The parents or guardian of the minor will be trained.

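### The between-group t test leaves the measured baseline unused or unspecified; baseline-adjusted ANCOVA is at least as efficient and costs only wording, but its gain depends on a correlation the protocol does not give

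*Protocol article*

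**What the plan says.** The analysis is in section 3.8 of the protocol article: "For the comparison between the groups, the *t* test will be carried out". The abstract names the same test. Neither place mentions a covariate, and neither says which variable is tested: the value at the end of treatment or the change from baseline.

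Baseline values will exist. For the primary outcome, section 3.1 states: "Nocturnal oximetry will be performed prior to treatment and post treatment". The opening of section 3 schedules the questionnaires, oximetry and orofacial assessments at baseline and after treatment. Sections 3.6 and 3.7 repeat this for the bruxism and sleep questionnaires.

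The planning figures are in section 2.4 and Figure 2. Section 2.4 plans "with 80% power and a significance level of 5%, considering the oxygen saturation index" and continues "with an effect size of 0.53, the minimum number per group should be 23 participants per group". Figure 2 gives the inputs as "Tail(s) = One; Effect size dz = 0.5373031" and the output as "Df = 22; Total sample size = 23; Actual power = 0.8027361".

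**The concern.** In a two-arm trial with a before-and-after measurement, three analyses of a continuous outcome are in common use: a t test on the final value, a t test on change, and ANCOVA of the final value on group and baseline. They estimate the same treatment effect with different precision. The first ignores baseline. The second subtracts it in full, which adds noise when the correlation between baseline and outcome is modest. ANCOVA uses baseline to the extent that the data support.

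Section 3.8 commits to a t test and leaves open which of the first two it is. With 46 children, chance differences in baseline saturation between the arms can be material, and a t test on final values carries them into the estimate. Precision matters here because 23 per group is small for the planning effect. The open choice of variable is also a choice that could be made after the data are seen.

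**Working it through.** **Inputs.** Effect 0.5373031 (Figure 2); 23 per group, 46 in total (sections 2.3 and 2.4); alpha 5% (section 2.4). Section 3.8 contradicts itself on alpha, "considering a level of significance of 0.5% (*P* < .05"; 5% is used here because it agrees with section 2.4. Two-sided testing is assumed. The correlation r between baseline and outcome is not in the protocol and is assumed at 0.3, 0.5 and 0.7.

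**Step 1: the plan's own figure.** One-sided paired t test, n = 23, df = 22:
- noncentrality = 0.5373 × √23 = 2.577
- critical t = 1.717
- power = 0.803

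This matches Figure 2 exactly. The figure of 23 is therefore the size of one paired sample, which section 2.4 then uses as the size of each of two groups.

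**Step 2: the planned two-group test.** Take 0.5373 as a between-group difference in units of the post-treatment SD. This is an assumption, because Figure 2 labels it dz. For a t test on post values:
- noncentrality = d × √(n/2) = 0.5373 × √11.5 = 1.822
- df = 44, two-sided critical t = 2.015
- power = 0.43

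**Step 3: change and ANCOVA on the same scale.**
- Change: SD is multiplied by √(2(1 − r)), so noncentrality = 1.822 / √(2(1 − r)), df 44.
- ANCOVA: residual SD is multiplied by √(1 − r²), so noncentrality = 1.822 / √(1 − r²), df 43.

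| r (assumed) | t test, post | t test, change | ANCOVA | share of gap from 43% to 80% closed by ANCOVA |
|---|---|---|---|---|
| 0.3 | 43% | 33% | 46% | 9% |
| 0.5 | 43% | 43% | 54% | 29% |
| 0.7 | 43% | 63% | 70% | 74% |

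Example at r = 0.5: noncentrality = 1.822 / √0.75 = 2.104, power 0.539; share = (0.539 − 0.430) / (0.800 − 0.430) = 29%.

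At r = 0, ANCOVA has 42.91% against 42.95% for the t test on post values, a loss of about 0.04 percentage points from the one degree of freedom. ANCOVA reaches 80% only at r of about 0.77.

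**Step 4: the other scale.** If 0.537 is instead in units of the SD of change, the t test on change has 43% at every r. For ANCOVA, noncentrality = 1.822 × √(2/(1 + r)):
- r = 0.3: 2.260, power 60%
- r = 0.5: 2.104, power 54%
- r = 0.7: 1.976, power 49%

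The gain over the t test on change now shrinks as r rises, but ANCOVA remains ahead. This is general: its residual variance relative to that of change is (1 − r²) / (2(1 − r)) = (1 + r)/2, which is below 1 whenever r is below 1.

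**The case against.** The strongest case against is that nothing here is an error. Under randomisation a two-sample t test on a continuous outcome is valid and unbiased over repeated allocations, and covariates are often left to an analysis plan, which is not at hand. The first half stands, and a reader should not infer that the planned test is invalid. The second half carries less weight: section 3.8 names a specific test, so the point is about a stated method and not about missing detail.

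Three stronger readings are tempting, and the protocol does not support them.

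- *Adjustment would recover much of the missing power.* This needs a correlation of about 0.6 or more (47% of the gap at 0.6), and the protocol gives none. It also needs a paired dz to be read as a between-group effect, and the t test to be on post values. If the test is on change, baseline is already used, and at r = 0.7 the gain on the first scale is only from 63% to 70%.
- *The t test is wrongly applied to categorical ratings.* Sections 3.2, 3.3 and 3.5 describe clinical evaluations without defining how they are scored. That they are categorical is inference.
- *Dentition phase must be a covariate.* It appears only in the eligibility criteria of section 2.2. Nothing links it to oxygen saturation, and no split between the phases is given. With an assumed even split, the arms would differ by 20 percentage points or more in about 24% of allocations; with a 16/30 split the figure is 12%. Adjusting for it is a preference.

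It is also fair to object that the low power comes from the sample-size calculation and not from the choice of test. That stands.

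**Conclusion.** The point holds as an efficiency and specification point. The planned t test is valid, but its variable is not stated and it is less efficient than adjusting for a baseline that will be measured anyway. On the assumption that 0.537 is a between-group effect in post-treatment SD units, with 23 per group and two-sided 5%, ANCOVA adds about 3, 11 and 27 percentage points over a t test on post values at r = 0.3, 0.5 and 0.7. Over a t test on change it adds about 14, 11 and 7. In SD-of-change units the gain over a t test on change is about 17, 11 and 6 points. The direction is secure on either scale, apart from the negligible loss at r near zero. The size is not, because neither r nor the scale of the effect can be taken from the protocol.

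A reader might infer that ANCOVA rescues the trial's power. It does not, unless r is about 0.77 or higher on the first scale. The one-tailed paired calculation applied to a two-group comparison is a separate defect and stays open.

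**What to change.** In section 3.8 (and the matching sentence of the abstract), replace the t test for oximetry and the other continuous or score outcomes with ANCOVA: end-of-treatment value on treatment group, adjusted for the baseline value of the same outcome. Name the end-of-treatment value as the analysed variable. Report the adjusted mean difference with a two-sided 95% confidence interval.

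The cost is wording and one degree of freedom; no extra participant, visit or measurement is needed. The change does not require a dentition covariate or a different test for the clinical ratings. Correct the sample-size calculation separately, for a two-group comparison; if it relies on baseline adjustment, it should state and justify the assumed correlation.

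### The significance level is written as 0.5% with P < .05 in brackets, two values ten-fold apart; 5% is almost certainly meant and should be stated

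*Protocol article*

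**What the plan says.** Section 3.8 (Statistical analysis) of the protocol article plans a t test between the groups, "considering a level of significance of 0.5% (*P* < .05"). The Methods part of the Abstract carries the same wording, so both descriptions of the analysis give the same pair of values.

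The level appears in two other places:

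- Section 2.4 (Sample calculation) sizes the trial "with 80% power and a significance level of 5" per cent.
- The Figure 2 caption, which reproduces the software output, gives α as "err prob = 0.05; Power (1" and so on. It also shows "Input: Tail(s) = One", "Effect size dz = 0.5373031", "Df = 22; Total sample size = 23" and "Actual power = 0.8027361".

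The article gives no reason for a level of 0.5%. It mentions no adjustment for multiple outcomes, no interim look and no stricter threshold for any endpoint.

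**The concern.** A level of 0.5% is a probability of 0.005, and P < .05 is a level of 5%. The two halves of the phrase therefore set different decision rules for the same test. This is the only significance criterion the article gives for the comparison between groups, and section 3.1 names nocturnal oximetry as the primary outcome to which it would apply.

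At stake is how a result between the two values is read. Any P value from .005 up to just under .05 meets the rule in the bracket and fails the rule in the percentage. A reader who takes the percentage literally would also find a trial analysed at a level ten times stricter than the one it was sized for.

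**Working it through.** **Step 1: set the four statements side by side.**

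| Place | Level stated | As a probability |
|---|---|---|
| Abstract, Methods | 0.5%, bracket P < .05 | 0.005 and 0.05 |
| Section 3.8 | 0.5%, bracket P < .05 | 0.005 and 0.05 |
| Section 2.4 | 5% | 0.05 |
| Figure 2 caption | α = 0.05 | 0.05 |

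0.05 / 0.005 = 10. Both brackets, section 2.4 and Figure 2 agree on 0.05. Only the percentage, in a phrase used twice, says otherwise.

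**Step 2: reproduce the article's own calculation.** The inputs are from the Figure 2 caption: dz = 0.5373031, n = 23, df = 22, one tail, α = 0.05. The output is that of a paired (one-sample) t test.

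- Noncentrality: δ = dz × √n = 0.5373031 × √23 = 2.576815. The caption gives 2.576815.
- Critical value: the 1 − α quantile of t on 22 df = 1.717144. The caption gives 1.7171444.
- Power: the probability that a noncentral t with 22 df and δ = 2.576815 exceeds 1.717144 = 0.802736. The caption gives 0.8027361.
- The smallest n with at least 80% power is 23, as stated.

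The output reproduces in full at α = 0.05, one-sided.

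**Step 3: change only α, to 0.005.** δ stays at 2.576815.

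- Critical value: the 0.995 quantile of t on 22 df = 2.818756.
- Power at n = 23: 0.424.
- Smallest n for 80% power: 44, against 23.

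The stated sample size and power therefore belong to 5%, not to 0.5%.

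**Step 4: size of the disputed zone.** On the same calculation, the chance that P falls between .005 and .05 when the planned effect is real is 0.803 − 0.424 = 0.379, or about 38 percentage points. This shows how far apart the two rules are. It does not forecast this trial's result, because the calculation is a paired one while section 3.8 plans a comparison between groups.

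**The case against.** The strongest reply is that the intended level can be recovered from the article. Section 2.4, Figure 2 and both brackets say 5%, and the sample size reproduces only at 5%. On that view 0.5% is a misplaced decimal point that would mislead few readers. The point about intent stands, and it limits the practical harm. It does not remove the contradiction: the phrase is wrong in both places where the analysis is described, and a decision threshold should not have to be inferred. Condensation for a journal does not explain it either, because the level is stated and stated wrongly.

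Three stronger readings are tempting, and the article does not support them.

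- *The investigators could pick the threshold once they know the result.* The lenient value is already the one in section 2.4, Figure 2 and both brackets. Switching to the other would only make success harder, so the slip offers little room for a favourable choice.
- *The trial has 43% power at 5% and 14% at 0.5%.* Those figures follow from a two-sided two-sample t test with 23 per group if 0.537 is taken as a between-group standardized difference. Figure 2 labels it dz, a paired effect size, and uses one tail. The fall from 80% to 43% comes from those two changes, not from the misprinted level.
- *The correction should also impose a two-sided 5% level throughout.* Section 3.8 gives no number of sides, which a condensed article may leave to the full protocol or analysis plan. Moving section 2.4 and Figure 2 to two-sided 5% would lower the power of the paired calculation at n = 23 to 0.69 and raise the required n to 30. That is a change to the sample size, not the correction of a misprint.

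**Conclusion.** The point holds as an internal contradiction in a figure the trial relies on: 0.005 and 0.05 are given as the same level in the Abstract and in section 3.8, and the first conflicts with section 2.4 and Figure 2. It is most likely a slip for 5%. That judgement rests on the agreement of every other statement of the level, and on the sample size output, which reproduces at 5% (power 0.803) and not at 0.5% (power 0.424). Both power figures take the Figure 2 inputs as given: paired, one-sided, dz = 0.5373, n = 23. They are used here only to show which level the planning used.

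The contradiction does not show that the sample size is wrong. The figure gives a total of 23 from a one-tailed paired calculation, while section 2.4 states that "the minimum number per group should be 23 participants per group". That mismatch, and the choice of one tail, need their own review.

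**What to change.** Replace 0.5% with 5% in the Methods part of the Abstract and in section 3.8, so that the percentage agrees with its own bracket, with section 2.4 and with Figure 2. This changes one number in two places. It needs no recalculation and does not alter the sample size.

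If 0.5% was in fact intended, the article should instead say so, give the reason, correct both brackets and redo section 2.4 and Figure 2. Nothing in the text points that way. The one-tailed input and the paired sample size calculation should be handled as a separate correction, because changing either one changes the number of participants.

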### 2.3. Experimental groups

Forty-six patients with sleep bruxism will be recruited and divided into 2 groups:

- CG which will undergo an application of placebo ILIB and an orofacial MFT exercise protocol;

- ILIB group, which will carry out an active application of ILIB and an orofacial MFT exercise protocol, this being once a week for 4 weeks.

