## 3. Outcome measures

All participants will undergo a parent or referent bruxism questionnaire, infant sleep quality questionnaire, nocturnal oximetry, and clinical assessment of orofacial functions at baseline and after 4 weeks of treatment. Patient retention and complete follow-ups are expected due to the treatment of bruxism symptoms.

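### Recruitment equals the stated minimum of 23 per group, so losses within the plan's own 5% ceiling would leave fewer than that minimum and slightly under 80% power on its own calculation

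*Protocol article*

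**What the plan says.** Section 2.4 (Sample calculation) states that "the minimum number per group should be 23 participants per group". Figure 2 shows the calculation behind it, with inputs "Tail(s) = One; Effect size dz = 0.5373031", a 5% error level and 80% target power. Its output is a sample of 23 with actual power 0.8027.

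Section 2.3 (Experimental groups) sets recruitment: "Forty-six patients with sleep bruxism will be recruited and divided into 2 groups". Section 2.1 gives the same total of 46.

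Two sentences deal with retention. Section 3 (Outcome measures) says "Patient retention and complete follow-ups are expected due to the treatment of bruxism symptoms". Section 3.8 (Statistical analysis) says "No loses greater than 5% of the sample are expected". Neither these sections nor Section 2.4 adds children to the 46 to cover losses.

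**The concern.** A minimum sample size normally means the number that must be available for analysis. Here the number recruited is the same as that minimum, while the analysis section accepts that some children may be lost. The plan's figures fit together only if every child completes, or if a lost child is replaced, on which the article is silent.

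The primary outcome makes this a practical matter. Nocturnal oximetry is recorded before and after treatment, with parents or guardians trained for it, so a child without a usable second recording has no post-treatment primary value. What is at stake is whether the stated minimum and the stated 80% power describe the data that will be analysed, and which retention figure actual losses will be judged against.

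**Working it through.** **Inputs**

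- Effect size dz = 0.5373031, one tail, alpha = 0.05, target power 0.80 (Figure 2).
- Minimum of 23 per group (Section 2.4).
- 46 recruited into two groups (Section 2.3), taken as 23 per group.
- Losses of at most 5% (Section 3.8).
- Section 3.8 gives the significance level both as 0.5% and as P < .05. I use 0.05, in line with Section 2.4.

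**Step 1: reproduce Figure 2.** For a one-tailed paired t test, the noncentrality is δ = dz × √n on n − 1 degrees of freedom. Power is the probability that a noncentral t exceeds the critical value. With n = 23, δ = 0.5373031 × √23 = 2.5768, critical t = 1.7171 on 22 df, and power = 0.8027. This matches the printed output.

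**Step 2: apply the loss ceiling.** 0.05 × 46 = 2.3, so two whole losses are within it. 46 − 2 = 44, split 22/22 or 23/21. Within one arm, 0.05 × 23 = 1.15, so one loss per arm (1/23 = 4.3%) is also within 5%.

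**Step 3: power on the document's own calculation**

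| n | δ | critical t | power |
|---|---|---|---|
| 23 | 2.5768 | 1.7171 | 0.8027 |
| 22 | 2.5202 | 1.7207 | 0.7861 |
| 21 | 2.4622 | 1.7247 | 0.7681 |

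So 23 is a true minimum, and one child fewer falls below 80%. At n = 22 the drop is 80.3 − 78.6 = 1.7 points, which is 80 − 78.6 = 1.4 points under target.

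**Step 4: power for the test that is planned.** Section 3.8 compares the groups with a t test. Assume, because the article gives no between-group effect size, that 0.5373 can be read as one. Then δ = d × √(n₁n₂/(n₁ + n₂)) on n₁ + n₂ − 2 df.

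| split | δ | one-sided power | two-sided power |
|---|---|---|---|
| 23/23 | 0.5373031 × √11.5 = 1.822 | 0.559 | 0.430 |
| 22/22 | 0.5373031 × √11 = 1.782 | 0.543 | 0.414 |
| 23/21 | 0.5373031 × √(483/44) = 1.780 | 0.542 | 0.413 |

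Two losses cost about 1.6 to 1.7 points here too. The gap between these figures and 80% comes from the choice of test in the calculation, not from attrition.

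**The case against.** The strongest reply is that the 5% is a ceiling on what is expected, not a planned attrition rate. A reader might infer that the plan's own figures necessarily take the sample below 23 per group. The text does not support that: with no losses the minimum is met, and the shortfall depends on losses occurring. This stands and limits the point.

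A reader might also infer that Sections 3 and 3.8 contradict each other on follow-up. They do not strictly do so. Zero loss satisfies both, and 5% is the only numerical benchmark, so the wording is loose rather than contradictory.

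Third, the effect is tiny. Section 2.4 describes the calculation "with an effect size of 0.53", and with that rounded value n = 23 already gives 79.3% before any child is lost. The shortfall is of the same order as the document's rounding. This stands as to size.

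Fourth, the 78.6% belongs to a one-tailed paired test, whereas the plan compares two groups. Figure 2 also labels its 23 as a total, and 44 children exceed that. The shortfall therefore appears only when 23 is read as a per-group minimum. But Section 2.4 itself makes that reading, and the number recruited rests on it. The objection does not remove the mismatch. It does show that quoting the paired power at 22 as the repaired figure would be misleading.

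Finally, an article may leave replacement of withdrawn children and the handling of missing data to the full protocol. That is fair, and nothing is asked on either.

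**Conclusion.** The point holds in a limited form. Recruitment is set at exactly the per-group minimum, and losses that the plan regards as within expectation would leave about 22 per group. On the document's own calculation, power would then be 78.6%, or 76.8% for an arm of 21 if both losses fall in one arm, against a stated 80%. This assumes equal allocation, analysis of children with complete data and no replacement of those lost.

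The shortfall is small and conditional, and it would not by itself change the trial. It is still worth correcting, because the article states both the minimum and the ceiling and recruitment leaves no room between them. The mismatch of test in Figure 2 is a larger and separate matter, but it determines how the power at 44 should be restated. The 54% and 41% rest on reading the paired effect size as a between-group one, which the document does not establish.

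**What to change.** Keep 46 randomised and make three changes of text.

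1. In Section 2.4, say that 23 per group is the number randomised and that losses of up to 5% would leave about 44 evaluable children, roughly 22 per group.
2. In the same place, restate the power at 44 for the between-group t test of Section 3.8, with its sidedness, significance level and between-group effect size given. Do not carry over the paired figure from Figure 2. If 0.5373 is kept as an assumed between-group effect size, the figure is about 54% one-sided or 41% two-sided.
3. In Section 3, replace the expectation of complete follow-up with the 5% figure, so that one retention benchmark applies throughout.

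The cost is wording and one recalculation, with no extra children. The printed power becomes less favourable: slightly so because of losses, and much more so because it would describe the planned test. Inflating recruitment to 23/0.95 = 24.2, rounded up to 25 per group, would restore the paired figure only. It would not give 80% for the between-group comparison, which under the same assumption needs 44 (one-sided) or 56 (two-sided) per group before losses.
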